# Financial Incentives Alone Versus Incentivized Partner Support for Promoting Smoking Cessation During Pregnancy and Postpartum: Protocol for a Non-Randomized Single-Blinded Study

**DOI:** 10.2196/resprot.7907

**Published:** 2017-10-31

**Keywords:** smoking, pregnancy, financial incentives, contingency management, partner support

## Abstract

**Background:**

Smoking tobacco remains the most significant modifiable cause of adverse pregnancy outcomes and contributor to ongoing maternal and infant ill-health. Pregnancy for many is a time of heightened health focus, with the primary motivation being the well-being of the unborn child. Yet, many women continue to smoke throughout their pregnancy. Despite this heightened motivation and known health risks, interventions to date have not effectively curbed the rate of smoking during pregnancy and they remain as high as rates among the general population. One promising strategy has been to incentivize these women to quit. However, incentives-based studies have not shown or reported long-term efficacy. Here, we present the protocol of a trial exploring the effect of incentivized partner support on pre- and postpartum smoking cessation.

**Objective:**

The aim of this study is to determine whether providing incentives to both the expectant mother and her support person in promoting short- and long-term smoking cessation during pregnancy is more effective than incentives to the expectant mother alone.

**Methods:**

This protocol is designed as a non-randomized, single-blinded trial to determine the efficacy of incentivized partner support, compared to participant incentive only, in promoting smoking cessation during pregnancy and postpartum. All eligible pregnant women receiving antenatal care via the Tasmanian Health Service (Australia) will be invited to participate. Participants will be eligible for monthly quit-contingent shopping vouchers if they verify, via carbon monoxide breath sample, as being abstinent from smoking. Participating women will be eligible for vouchers until 6-months postpartum and will be followed up at 12-months postpartum.

**Results:**

The recruitment phase of this study has concluded. Results are expected to be published by the end of 2018.

**Conclusions:**

This study protocol extends the current literature on incentivized smoking cessation interventions for pregnant women by assessing the influence of incentivizing a support partner on short- and long-term abstinence. Key ethical considerations are discussed including potential for receipt (or not) of quit-contingent vouchers impacting negatively on the participant’s relationship with their partner. The findings of the study may have important implications for the role support partners are assigned in smoking cessation programs targeting pregnant women.

**Trial Registration:**

Australian New Zealand Clinical Trials Registry (ACTRN): 12615001158550; https://www.anzctr.org.au/ Trial/Registration/TrialReview.aspx?id=367981 (Archived by WebCite at http://www.webcitation.org/6tGKO28uh)

## Introduction

### Smoking and Perinatal Health

Smoking during pregnancy is recognized as the single most modifiable cause of poor pregnancy outcomes [1] and the risks to mother and baby have been reported extensively elsewhere [2]. Briefly, these risks include increased risk of miscarriage, preterm birth, low birth weight, major congenital abnormalities, and sudden infant death syndrome [2,3]. Less known long-term effects as a result of prenatal smoke exposure include increased risk of reduced neuromotor function, attention deficit hyperactivity disorder (ADHD), learning difficulties, and behavior dysregulation during childhood and adolescence [4-7]. Infant exposure to second-hand smoke has also been shown to further compound these negative health consequences [2]. Despite these known risks, many women continue to smoke during and after pregnancy, at rates comparable to the general smoking population [8,9]. Even when women manage to quit during pregnancy, most (up to 80%) relapse within 6 months of delivery [10]. Rates are considerably and consistently higher among certain already disadvantaged cohorts including young expectant mothers (in Australia, 34% of pregnant women 20 years or younger smoke) and women living in rural and remote areas (37% in Australia) [11]. More effective, targeted interventions are clearly needed for this high-risk group.

### Interventions for Promoting Cessation Among Pregnant Smokers

One of the most effective strategies for promoting smoking cessation among pregnant women is incentives-based interventions [12,13]. Providing incentives for pregnant smokers to quit has been shown to not only increase abstinence rates several-fold compared to any other type of treatment, but also to increase mean birth weight [12,14]. Further, in a review of the most common interventions (including cognitive behavior therapies, stages of change, feedback, pharmacotherapies, and other therapies), incentives-based programs were found to be the most cost-effective, producing a net cost benefit of US $3482 after factoring in intervention costs [12,15,16]. Incentives-based programs for pregnant smokers appear to promote successful postpartum abstinence rates (approximately 25% abstinent at 3 to 6 months postpartum), but since few studies have included long-term postpartum follow-up, the long-term efficacy is not well understood [17]. While one study reported a 12-month postpartum follow-up with promising cessation rates (0% to 44% depending on model of care), this study included participants who had quit within 1 month of enrolment, and thus the effectiveness of incentives-based interventions at promoting long-term abstinence remains unclear [18].

### Partner Support and Sustained Cessation

In a review of postpartum relapse prevention strategies, programs that involved the pregnant smoker’s partner were deemed necessary to maximize long-term cessation success [19]. To date, only one randomized controlled trial (RCT) has been conducted to examine the effect of partner support [20]. Participants were randomized to 3 groups: usual care, counseling support (6 counseling telephone calls; 3 during pregnancy, 3 postpartum), and counseling support combined with partner-support facilitated by a tailor-made “it takes two” booklet and video (partner was usually baby’s father who was also provided 6 separate counseling support telephone calls). No significant difference in participants’ smoking behavior was found between the groups. Interestingly, the authors found that positive support (behaviors characterized by cooperation and reinforcement of quitting behavior such as “compliment you on not smoking”) diminished linearly from baseline to 12 months postpartum and negative support (behaviors characterized by nagging and policing such as “comment on your lack of willpower”) decreased through pregnancy before increasing again postpartum.

The importance of the quality of support provided in partner support interventions has been found to be critical in promoting cessation among non-pregnant smokers [21]. In a study exploring the effect of positive and negative support behaviors on quit rates among female smokers, Cohen and Lichtenstein showed that women who reported receiving a higher ratio of positive supportive behavior compared to negative (using a shortened version of the Partner Interaction Questionnaire) from their spouse were more likely to quit. This emphasis on quality of support may explain why other studies found no effect for partner support [20-22].

Combining incentives programs with partner support, particularly the co-habiting and/or romantic partner (eg, expectant father) that emphasizes positive support, may therefore be an approach that fosters more effective long-term cessation for pregnant smokers. To our knowledge, only one study to date has explored incentivizing social support to promote smoking cessation in pregnant women. Donatelle and colleagues [23] compared 2 groups: 1 receiving usual antenatal care and 1 which included both the women and their chosen female non-smoking supporter (providing unstandardized, non-formalized, “natural” peer support only) provided with quit-contingent shopping vouchers. Participants in the incentivized partner support group were more likely to be quit at the end-of-pregnancy (32% versus 9%) and at the 2-month postpartum (21% versus 6%) time points compared to usual care. Since this study was not fully factorial (eg, intervention groups consisting of social support only and incentives only, not included), the effect of partner support over and above incentives could not be determined. Furthermore, the support person in the Donatelle et al [23] study was not the pregnant women’s spouse (eg, husband and/or father of child), but rather a female, non-smoking friend, who might arguably have had less vested interest in the health of the expectant child than the expectant father.

### Objectives

The purpose of this study is to determine whether providing incentives to both support person and expectant mother, if she is able to quit smoking, is more effective than providing incentives to expectant mother only, in promoting short- and long-term smoking cessation during pregnancy. In essence, the present study seeks to answer the question: “Can partners (eg, spouse) be incentivized to be more supportive and effective quit buddies to their pregnant smoking partners?”

Specifically, the study aims to determine whether (1) providing an incentive to both the support partner and expectant smoking mother to quit is more effective than providing an incentive to the pregnant smoker alone at promoting abstinence; (2) regardless of incentives, women who receive more positive cessation support from their partners, as measured by the Partner Interactive Questionnaire 20 (PIQ-20), are more likely to quit smoking; and (3) providing incentives for pregnant smokers to quit is more effective than “usual care” antenatal quit smoking services such as brief advice and referral to smoking cessation services (external telephone counseling and smoking cessation nurse) at promoting smoking cessation.

The primary outcome for the study is smoking status (ie, smoking or quit), as determined by self-report 7-day point prevalence, and carbon monoxide (CO) less than 7 particles per million (ppm) at the end-of-pregnancy time point. Secondary outcomes include effect of incentives on long-term (2 months and 12 months postpartum) abstinence and influence of the quality of partner support (positive compared to negative supportive behaviors) on smoking status.

## Methods

### Trial Design

This study will adopt a non-randomized, single-blinded, controlled 2-group (control and treatment) trial design.

### Participant Recruitment

All eligible pregnant women who smoke and live in Tasmania (Australia) are invited to participate in the study. Statewide recruitment is facilitated by drawing on data from the Tasmanian Health Service’s digital medical record (DMR) and encompasses multiple strategies to maximize reach. A research midwife, with access to the Tasmanian Health Service’s DMR, conducts “cold calling” of all women who self-reported smoking in the last 7 days during their initial antenatal “booking in” appointment (usually around 10 weeks gestation). Using information stored on the DMR, the midwife pre-screens women for eligibility (eg, self-report smoking, 16 years or older) and telephones them to invite them to participate in the study. With their verbal consent, the details of interested women are recorded and forwarded to the research team.

Antenatal staff of the Tasmanian Health Service (including physicians and midwives) provide study information (in the form of a flyer) to eligible participants during antenatal appointments. With their consent, the contact details of interested women are forwarded to the research team. In addition, the study is advertised through flyers placed in general practitioner (GP) clinics, outreach centers and community hubs across Tasmania. Informal advertising via social media (eg, Facebook) and television and radio interview exposure may also be utilized. Consequently, potential participants could also self-refer to the study by contacting the researchers directly.

### Eligibility Criteria

Women who express interest in participating in the study (either self-refer or consent to a health professional forwarding their contact details to research staff) are contacted by research staff and screened for eligibility using a previously validated protocol [24]. To be eligible for study entry, women must be (1) pregnant (20 weeks gestation or less); (2) at least 16 years of age; (3) self-report as being a current smoker (“even a single puff in the last 7 days”); (4) attending routine antenatal care provided by the Tasmania Health Service or participating GP center (Tasmanian, Australia); and (5) be able to attend a minimum of 3 appointments at 1 of the 3 data collection sites across Tasmania (Launceston General Hospital, Royal Hobart Hospital, or Mersey Community Hospital). Women younger than 18 years (but 16 years or older) require the consent of their parent, guardian, or senior antenatal health provider to participate in the study.

Potential participants are excluded from study entry if they self-report as non-smoking (ie, “have not smoked, even a single puff in last 7 days”) or if they have a cognitive or intellectual impairment that will inhibit fulfillment of participation requirements (eg, completion of surveys and/or attend organized study appointments). Participants who are found to be “gaming” (eg, those who tell researchers they are pregnant and/or smoking untruthfully to enroll in study) are also excluded from further participation and their data discarded. All participants are asked to nominate and are encouraged to bring along to study visits a support person, preferably a person they co-habit with (eg, spouse, father of child, or family member).

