### Interventions

During their initial enrolment visit (visit 1), all participants and their support partners are offered a separate resource pack providing further information and quit references. The content of the packs, selected on the basis of existing resources developed and distributed by not-for-profit organizations and government-funded bodies (eg, Quitline, Cancer Council, and SIDS and Kids), includes informational brochures on the topics of smoking and pregnancy, quitting smoking during pregnancy, a guide for quitting smoking, and smoking and sudden infant death syndrome. A referral and resources summary list (eg, further websites and available mobile phone apps) is also provided that includes telephone numbers of local counseling services. The resource pack specifically designed for partners contains information about the effect of second-hand smoke on children, quit smoking products, and how to be an effective quit buddy. Following the single-blinded, consecutive-month schedule, women are allocated to either the control or treatment group during their enrolment session (Textbox 1).

Control and Treatment group incentives.GroupControlOnly the participant is rewarded with a AUD $50 voucher if they verify as quit during monthly visitsTreatmentBoth participant (1 x AUD $50) and their designated support person (1 x AUD $50) receive a shopping voucher if the participant verifies as quit during monthly visitsIf partner is not present during study visits, participant collects both vouchers

All participants are encouraged to make a quit attempt in the 2 weeks following the enrolment visit in order to promote quit status (verified by less than 7 ppm CO breath sample) and enable incentive issue at the first monthly follow-up, although it is emphasized that each participant is able to decide their own quit timeframe and approach. No other formal smoking cessation counseling support is provided.

All participants are asked to attend 2 further study visits—visit 2 (end-of-pregnancy) and visit 3 (end-of-study)—and have the opportunity to attend monthly visits to verify their non-smoking status and receive incentive voucher/s.

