### Verification of Smoking Status

During each visit and telephone call, participants are asked if they have smoked, even a single puff, in the last 7 days. During study visits, participants complete a 14-day timeline follow-back questionnaire as an assessment of self-reported smoking. To verify self-report, all participants are required to provide 2 expired air CO samples using a piCO Simple Smokerlyzer [25]. Expired CO was chosen as the most appropriate biochemical verification method in this study as it is not sensitive to the use of nicotine-containing medication (such as nicotine replacement therapy which may be used by participants), is non-intrusive, immediate (facilitates immediate provision of quit-contingent incentive vouchers), and inexpensive. The CO readings are recorded and if the average of the 2 samples is less than 7 ppm, the participant’s smoking status is recorded as quit and she receives a voucher incentive. A cut-off value of less than 7 ppm was selected based on recommendations from the National Institute of Health and Care Excellence [15], in addition to the precedent set by existing research in the field which accounts for likely second-hand smoke exposure (eg, from support partner) [18,26]. To check whether our results are sensitive to the CO cut-off value, we also repeat our primary analysis using a CO level of less 4 ppm as the cut-off for abstinence. Substantial discrepancies between the results obtained with the 2 cut-off values suggests that participants are “gaming” the system (that is, continuing to smoke but cutting down just enough to receive the abstinence reimbursement). Based on results of previous similar studies [27], we do not expect “gaming” among participants for incentives to be a significant issue.

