#### Enrolment Visit

During the enrolment visit (visit 1) participants are asked to complete a battery of questionnaires and provide 2 CO breath samples. Regardless of group allocation, participants are asked to nominate a support person (they are asked to have this person in mind when completing the Partner Interaction Questionnaire), preferably the person they are living with (eg, partner or family member), whose contact details are recorded along with the participant’s own details to assist with future correspondence. While no smoking cessation counseling is provided, participants are offered a resource pack for themselves and their support partner.

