#### Monthly Telephone Calls and Verification Visits

Monthly telephone calls are conducted with all participants to determine smoking status. During the phone calls, participants are asked “Have you had a cigarette (even a puff) in the past 7 days?” If a participant self-reports as abstinent, they are invited to attend a follow-up verification visit to verify their smoking status (and receive a voucher incentive), which is booked at their next convenience. If the participant self-reports smoking in the last 7 days during the monthly telephone call, they are advised that they are not eligible for the incentive that month and will be contacted again the following month. This monthly payment schedule limits the additional participation burden on participants, and where possible, is scheduled on days when they are attending routine hospital antenatal appointments. This monthly payment schedule was also utilized by the only other study published using incentivized partner support [23]. Participants who verify as abstinent at their end-of-study visit (visit 3) are eligible to receive monthly calls and incentives until 6 months postpartum. Participants who are still smoking at the end-of-study visit no longer receive monthly calls (and are ineligible for any further incentives) from that date. Multiple (up to 5) attempts are made to contact each participant for their scheduled monthly telephone calls and visits. Text messages (short message service, SMS) are also utilized to try to contact those difficult to reach. However, the study adopts an intention-to-treat approach such that if participants become un-contactable at any time throughout the study, it is presumed they are smoking [28].

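### Women found to be gaming are removed after allocation and their data discarded, with no limit to entry facts and no masking of the decision, so any effect on the quit-rate comparison cannot be checked

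*Protocol article*

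**What the plan says.** Eligibility Criteria treats two groups differently. Potential participants who do not qualify are kept out of the study. Participants found to be gaming "are also excluded from further participation and their data discarded". Gaming is explained there only through an example: "those who tell researchers they are pregnant and/or smoking untruthfully to enroll in study". The smoking criterion itself is that a woman "self-report as being a current smoker", where one puff in the past week is enough.

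Under Interventions, "women are allocated to either the control or treatment group during their enrolment session". At that same visit women "complete a battery of questionnaires and provide 2 CO breath samples", but the article does not link the CO result to eligibility or to a finding of gaming.

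Trial Design describes a "non-randomized, single-blinded, controlled 2-group (control and treatment) trial design". Assignment of Interventions explains the blinding as blinding of participants. Monthly Telephone Calls and Verification Visits states that "the study adopts an intention-to-treat approach" and spells this out for women who cannot be contacted, who are presumed to be smoking.

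Verification of Smoking Status uses the word gaming in a second sense: "continuing to smoke but cutting down just enough to receive the abstinence reimbursement". It addresses that behaviour by repeating the primary analysis with a 4 ppm cut-off.

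**The concern.** A woman with study data to discard has, as a rule, already been allocated. The rule therefore re-judges eligibility after allocation. It sets no time limit, does not require that the evidence predate follow-up, and does not keep the person deciding unaware of the arm or of later smoking status.

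These removals are not neutral to the outcome. A woman who was not smoking at entry and stays that way reports abstinence and passes the CO test below 7 ppm, so she counts as a quitter. Discarding her removes one success and one woman from her arm. If false entrants are found and removed more readily in one arm than in the other, the difference in quit rates moves for a reason unrelated to the intervention. This affects the end-of-pregnancy comparison (Hypothesis 1) and the two postpartum comparisons (Hypothesis 2).

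Discarding the data makes the problem irreversible. No one could later re-judge the decisions or rerun the comparison with these women included.

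**Working it through.** **What the documents give.** They state no number of gaming exclusions and no assumed quit rates, so there is no planned figure to reproduce on this point. The one figure borrowed is the total sample size of 108 (Sample Size and Checks; Hypothesis 1). It is used only to set the scale, and its derivation does not matter here.

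**Assumptions.** Equal arms, 108/2 = 54 each; two-sided alpha of 0.05 (not stated in the article); the planned chi-square test on a 2 x 2 table, which equals the pooled test

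z = (p_T − p_C) / sqrt[ p(1 − p)(1/n_T + 1/n_C) ], where p is the pooled quit rate.

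**Step 1: shift in one arm's quit rate.**
- Five discarded women recorded as quit: 20/54 = 37.0% becomes 15/49 = 30.6%, a fall of 6.4 points.
- Three discarded at an expected rate of 20%: (10.8 − 3)/(54 − 3) = 7.8/51 = 15.3%, a fall of 4.7 points.

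**Step 2: two records can move a borderline result in either direction.**

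| Treatment | Control | z | p |
|---|---|---|---|
| 18/54 | 10/54 | 0.1481/0.0843 = 1.757 | 0.079 |
| 18/54 | 8/52 (two control quitters discarded) | 0.1795/0.0836 = 2.147 | 0.032 |
| 20/54 | 10/54 | 0.1852/0.0862 = 2.148 | 0.032 |
| 18/52 (two treatment quitters discarded) | 10/54 | 0.1610/0.0857 = 1.879 | 0.060 |

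**Step 3: type I error when only one arm loses records.** Both arms have the same true quit rate, k recorded quitters are discarded from one arm and none from the other, and the probability of rejection is summed over all pairs of binomial counts.

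| True quit rate | k = 0 | k = 1 | k = 2 | k = 3 | k = 5 |
|---|---|---|---|---|---|
| 10% | 0.050 | 0.080 | 0.132 | 0.234 | 0.467 |
| 20% | 0.051 | 0.060 | 0.084 | 0.120 | 0.247 |
| 30% | 0.050 | 0.056 | 0.068 | 0.089 | 0.152 |
| 40% | 0.049 | 0.053 | 0.062 | 0.074 | 0.113 |

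Removal from one arm only is the worst case. Part of the rise also comes from fixing k: with three quitters discarded from each arm at 20%, the same sum gives 0.089, split evenly between the two directions (about 0.044 each). The directional part is the better measure of bias. At 20% with k = 3 in one arm, false rejection in favour of the untouched arm rises from 0.025 to 0.113.

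**Step 4: what creates the bias.** Under equal true quit rates, equal removal favours neither arm. Removing every false entrant accurately in both arms would do no harm. The bias comes from unequal detection or judgement, and the stated rule has no guard against that.

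**The case against.** The strongest reply is that the sentence concerns entry fraud. It stands under Eligibility Criteria, both of its examples are lies told to get in, and removing women who were never eligible, on facts that predate allocation, is defensible. A lie told in order to enrol also comes before the woman could know her arm, so the plan gives no reason for false entry itself to differ by arm. False pregnancy can be checked objectively, because the research midwife works from the digital medical record (DMR). The detailed procedure may be in the full protocol. All of this stands. It supports a narrow, masked rule with retained data, whereas the text states an open one that deletes the data.

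Some stronger readings are tempting but unsupported:

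- *Staff may discard a woman because of her follow-up CO pattern.* The open example does not expressly rule this out, but Verification of Smoking Status defines that behaviour separately and answers it with the 4 ppm rerun. It provides for no removal, and the rerun needs these women's data.
- *The expectation of little gaming cannot be verified.* That expectation concerns the CO threshold, which the rerun examines on retained data.
- *The decision is made by staff who know the arm, and suspicion falls on the treatment arm.* The article names no decision-maker. Calendar-block allocation and arm-specific vouchers make knowledge of the arm plausible, but it remains an inference, and nothing in the text supports greater suspicion of one arm.
- *The intention-to-treat rule is broken.* The only detail given concerns women who cannot be contacted. Deleting allocated women's data fits poorly with the stated approach, but it does not contradict that detail.

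**Conclusion.** The point holds in a limited form. The article states a removal that acts after allocation, is defined only by example, is not confined to entry facts, is not described as masked, and destroys the data. Because a false smoker would normally be recorded as quit, removals that differ by arm would bias the Hypothesis 1 and 2 comparisons, and nobody could later show whether they had.

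The size is unknown and may be small. The figures above are illustrations that rest on 54 women per arm, assumed quit rates and discards concentrated in one arm. They show that two or three records can matter at this sample size, not that they did. The direction is also open: discarding control quitters favours the treatment arm, and discarding treatment quitters works against it. A reader should not infer a demonstrated bias, or a rule that removes women for their outcome.

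**What to change.** In Eligibility Criteria:

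1. Limit exclusion for gaming to false entry facts (not pregnant, or not a smoker at entry), shown by information dated at or before visit 1 or by the DMR. A low visit 1 CO reading alone cannot disprove one puff in the past week, so it should not suffice by itself.
2. Have the decision made by someone masked to arm and to follow-up smoking status.
3. State that the CO pattern described in Verification of Smoking Status is never a ground for removal.
4. Retain all data and report exclusions by arm with reasons.
5. Present the Hypothesis 1 and 2 comparisons both with and without the excluded women. Whether proven false entrants belong in the main count is debatable, which is why both are needed. Say in advance how a woman who was never pregnant is counted, since she has no end-of-pregnancy outcome.

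The cost is minor wording, a masked check of a few records and one extra analysis. Recruitment has closed but postpartum data collection continues, so retention, masked review and reporting by arm remain possible for records still held. No stated figure changes.
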